#### Laboratory assessment

Lipid profiles (total cholesterol, HDLc, TG, apolipoprotein A-1, and apolipoprotein-B), hs CRP, metabolic markers (fasting blood sugar and hemoglobin A1c), renal and hepatic function, and creatine phosphokinase (CPK) will be measured at baseline and after 12 months. At both baseline and after 12 months, sampled blood will be collected in ethylenediamine tetraacetic acid (EDTA) bottles, centrifuged for 15 min at 1000 g, and stored in a freezer at temperatures below − 70 °C. Using stored plasma, the levels of adiponectin, lipoprotein-associated phospholipase A2, and fatty acid binding protein will be measured at the end of the study using specific ELISA kits.

#### Study endpoints

The primary endpoint of this study is the comparison of the change in percentage NCV and absolute NCV between statin plus fenofibrate and statin alone groups of non-diabetic, combined dyslipidemia patients with non-intervened intermediate coronary artery disease at 12 months. The secondary endpoints are as follows: 1) comparisons of the changes in other tissue components of percentage and absolute plaque volume in index non-intervened lesions, including DC, FF, and F; 2) change in plaque phenotypes such as TCFA; 3) change in grey IVUS parameters, including vessel area/volume, lumen area/volume, plaque area/volume, and remodeling index; 4) MACEs for 12 months, including all cause death, CV death, nonfatal myocardial infarction, stroke, and ischemia-driven revascularization of intervened and non-intervened lesions; 5) relationships between the changes in tissue components of plaque and changes in laboratory findings; 6) adverse reactions to the study drugs, including myalgia, elevation of CPK more than twice the upper limit of normal, and hepatic dysfunction (alanine aminotransferase more than three times the upper limit of normal).

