**Methods/design:**

The STAFENO trial is a prospective, randomized, open-label, multi-center trial to compare the effect of statin plus fenofibrate with statin alone on the reduction and stabilization of plaque in non-diabetic, combined dyslipidemia patients with non-intervened, intermediate coronary artery disease (CAD) using virtual histology-intravascular ultrasound at 12 months. A total of 106 eligible patients are planned to be randomized to receive either a combination therapy (rosuvastatin 10 mg plus fenofibrate 160 mg/day) or monotherapy (rosuvastatin 10 mg/day) for 12 months. The primary endpoint of this study is the percentage change in the necrotic core volume. Secondary endpoints include changes in tissue characteristics and 1-year major CV events, including all-cause mortality, CV mortality, nonfatal myocardial infarction, stroke, and revascularization of the intervened and non-intervened lesions.

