### Study objectives and hypotheses

The primary objective of this study is to compare the changes in percentage necrotic core volume (NCV) and absolute NCV in non-culprit intermediate lesions in non-diabetic, combined dyslipidemia patients after 12 months’ therapy with statin plus fenofibrate compared to statin alone. The working hypothesis of this trial is that statin plus fenofibrate combination therapy is superior to statin alone therapy in reducing the 12-month percentage NCV and the absolute NCV. The secondary objective is to compare changes in percentage and absolute dense calcium (DC), fibrofatty (FF) and fibrous (F) plaques, the incidence of and changes in thin cap fibroatheroma (TCFA), the changes in variables of grey scale IVUS (volumes of external elastic membrane, lumen, and plaque), and the remodeling index between the statin plus fenofibrate and statin alone groups. In addition, secondary endpoints will include comparisons of major adverse cardiac events (MACEs) at 12 months, defined as all-cause death, CV death, nonfatal myocardial infarction (MI), stroke, and ischemia-driven revascularization of intervened and non-intervened lesions between the two groups. In order to identify the mechanisms of plaque stability and regression, the relationships between the variables of the VH-IVUS parameters and laboratory markers, including lipids, inflammatory markers, and metabolic markers, in the statin plus fenofibrate and statin alone groups will be investigated. The incidence of drug adverse effects will be another secondary endpoint of the study.

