## Statistical considerations

### Sample size calculations

Based on a previous study [15], a sample size of approximately 42 patients per treatment group was calculated to provide 80% power (assuming a standard deviation of 7.82) to detect a difference of 4.78 in percentage NCV and to detect the superiority of statin plus fenofibrate compared to statin alone with a two-sided alpha level of 0.05. With a statin plus fenofibrate:satin alone sampling ratio of 1:1 and a dropout rate of 20%, a final sample size of 53 patients per treatment group (total 106 patients) was specified in order to provide an adequate number of evaluable patients. To the best of the researchers’ knowledge, no study has been conducted on the change of tissue characteristics after fenofibrate treatment. We hypothesized that fenofibrate has an effect on percentage NCV as much as that of 10 mg atorvastatin [15]. In addition, a previous study [16] consisting of 100 patients with non-significant lesions demonstrated a significant decrease in NCV in the rosuvastatin (10 mg/day) treated group but not in the simvastatin treated group (20 mg/day).

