### Statistical analyses

The primary endpoint of percentage NCV and absolute NCV will be analyzed using a paired-sample *t*-test or Wilcoxon rank-sum test for changes within each group, and an unpaired *t*-test or Mann–Whitney U test for differences between the two groups. Continuous variables will be expressed as mean ± standard deviation and compared by either a Student’s *t*-test or Mann–Whitney U test based on whether or not the data are normally distributed. Categorical variables will be expressed as number or percentage and compared by χ^2^ or Fisher’s exact test. Pearson correlation test will be used to evaluate the correlation between the changes in percentage NCV and absolute NCV, and changes in laboratory findings from baseline to follow-up. These statistical analyses will be performed in the entire index non-culprit segment and the most severe 10-mm segment centered on the minimal lumen area.

Multivariable linear regression analysis will be performed in order to identify the independent predictors of the reduction in percentage NCV. To analyze the secondary endpoints, VH-IVUS parameters, grey IVUS parameters, and angiographic parameters will be analyzed using a paired sample *t*-test or Wilcoxon rank-sum test for changes within each group, and an unpaired *t*-test or Mann–Whitney U test for differences between the two groups. Correlations between these parameters and laboratory variables will be evaluated by the Pearson correlation test.

Changes in the phenotypes of the index lesions between the two groups will be compared by χ^2^ or Fisher’s exact test. The composite endpoint of CV events will be analyzed by comparing the Kaplan–Meier event rates using a log-rank test. A *p* value < 0.05 will be considered statistically significant.

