### The rationale for VH-IVUS-measured percentage NCV as a primary endpoint

The PROSPECT trial revealed that non-culprit lesions account for a substantial proportion of future CV events [5]. Independent predictors for future CV events were a plaque burden ≥ 70%, VH-IVUS-proven TCFA, and a minimum lumen area ≤ 4.0 mm^2^. Similarly, the VIVA study revealed that such predictors were related to a high degree of angiographic diameter stenosis, which may explain why subsequent clinical events were linked to baseline non-culprit lesion severity [33]. As these data prove VH-IVUS as a legitimate in vivo diagnostic modality for delineating the relationship between non-culprit lesions and CV events, we decided to use VH-IVUS to track the quantitative change in NC and the characteristic change in TCFA in both treatment arms.

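### Two necrotic core variables are primary, each at p < 0.05 and with no segment named as primary, but the sample size covers one test and other parts of the article name a single primary endpoint.

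*Protocol article*

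**What the plan says.** Three sections of the protocol article make two variables primary.

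- Study endpoints: "The primary endpoint of this study is the comparison of the change in percentage NCV and absolute NCV".
- Study objectives and hypotheses: the primary objective is "to compare the changes in percentage necrotic core volume (NCV) and absolute NCV in non-culprit intermediate lesions", and the working hypothesis is that the combination is "superior to statin alone therapy in reducing the 12-month percentage NCV and the absolute NCV".
- Statistical analyses: the primary analysis is described for both variables, with an unpaired t-test or Mann–Whitney U test between groups. The paragraph ends: "These statistical analyses will be performed in the entire index non-culprit segment and the most severe 10-mm segment centered on the minimal lumen area". The only significance rule is that a p "value < 0.05 will be considered statistically significant".

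Three other places point to a single primary.

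- Abstract, Methods/design: "The primary endpoint of this study is the percentage change in the necrotic core volume".
- Discussion, a subsection headed: "The rationale for VH-IVUS-measured percentage NCV as a primary endpoint".
- Sample size calculations: the trial is sized "to detect a difference of 4.78 in percentage NCV", with SD 7.82, two-sided alpha 0.05 and 80% power. No difference or SD is given for absolute NCV, and no segment is named.

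**The concern.** The identity of the primary endpoint decides whether the trial is positive, and the article gives more than one answer. Its operating characteristics (5% alpha, 80% power) were worked out for a single test, while the endpoint section names two variables and the analysis section runs each in two segments.

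What is lost depends on how success is declared. If either variable is enough, the false-positive rate exceeds 5%. If both are needed, power falls below 80%.

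The two variables can also disagree, because percentage NCV has plaque volume as its denominator. As an invented illustration, suppose a plaque of 100 mm³ with 20 mm³ necrotic core becomes 84 mm³ with 19 mm³. Absolute NCV falls by 5%, while percentage NCV rises from 20.0% to 19/84 = 22.6%. This shows only that disagreement is possible. If it happened, the article would give no primary answer, and the choice could be made after the results were seen.

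**Working it through.** **Inputs.** From Sample size calculations: difference 4.78, SD 7.82, 42 per group, 80% power, two-sided 0.05, 20% dropout, 53 per group. From Study endpoints and Statistical analyses: two variables, two segments, threshold 0.05. Assumed, because the article does not give them: the correlation between test statistics (0 to 0.95), and 80% power for absolute NCV.

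**Step 1: reproduce the plan's figure.**

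n = 2 × SD² × (1.960 + 0.842)² / difference² = 2 × 7.82² × 2.802² / 4.78² = 42.0 per group.

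Dropout: 42 / 0.8 = 52.5, rounded up to 53, so 106 in total. Power at 42 per group is 80.0% by the normal approximation and 79.1% by the t-test. The sizing is sound for one test.

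**Step 2: two variables, one segment.**

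- Either counts, independent tests: 1 − 0.95² = 9.75%.
- Both required, independent tests, 80% each: 0.80² = 64%.
- Correlated tests: the same two probabilities from the bivariate normal distribution.

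| Assumed correlation | Type I error if either counts | Power if both required |
|---|---|---|
| 0 | 9.75% | 64% |
| 0.5 | 9.1% | 69% |
| 0.8 | 7.8% | 73% |
| 0.9 | 7.0% | 75% |
| 0.95 | 6.5% | 76% |

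When both are required, type I error stays at or below 5%. Joint power cannot exceed the power of percentage NCV alone (80%), whatever the effect on absolute NCV. It would be lower than shown if absolute NCV had less than 80% power.

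**Step 3: if both segments also counted as primary.**

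That makes four between-group tests. Any one sufficient, independent: 1 − 0.95⁴ = 18.5%. By simulation with correlation 0.9 between variables and 0.9 between segments: about 10%. With all four equally correlated at 0.95: about 8%.

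**Step 4: the repairs.**

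- One variable in one segment as sole primary: the Step 1 figures apply unchanged.
- Two primaries with alpha 0.025 at the first step: power per variable at 42 per group is 69.7% by the t-test (71.2% by the normal approximation), assuming the standardised effect 4.78 / 7.82 = 0.61 for each.

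**The case against.** The strongest counter-argument is that the single-primary reading is available. The sample size, the rationale heading and the regression for predictors of response all concern percentage NCV. On that reading, in one segment, 5% and 80% both hold. Testing order, alpha allocation and the choice of segment are also often left to a full protocol or analysis plan, and neither is shown here. This stands in part: the lack of a written success rule would not be a finding on its own. It does not remove the conflict. The objectives, endpoint and analysis sections positively state two primaries, and the abstract and rationale heading state one. A document not shown cannot make these agree.

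Three stronger readings may tempt a reader, and the article does not support them.

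- That there are four primary tests. Nothing labels the 10-mm results primary; the endpoint section names no segment, and the 10-mm analyses could be supportive. The four-test figures are conditional.
- That 5% alpha and 80% power cannot both hold. Which one fails depends on the success rule, and by how much depends on correlations the article does not give. High correlation is plausible, since both variables share the necrotic core measurement, and the effect is then modest.
- That the winner could be picked after unblinding. The trial is open-label with a blinded image reader, so the relevant moment is when between-group results are first seen.

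The abstract's wording, taken literally, is a relative change in absolute volume and so a third quantity. It may only be loose wording for change in percentage NCV; the text does not settle it.

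**Conclusion.** The point holds in this limited form. The article is inconsistent about its primary endpoint, and its sample size matches only one of the definitions it gives. With two primaries, type I error is about 6.5% to 9.75% if either suffices. If both are required, which is how the hypothesis reads most naturally, alpha is kept but power is about 64% to 76%, with a ceiling of 80%. If both segments also counted, which the text leaves open, any-of-four error would be about 10% to 18.5%, or about 8% at a correlation of 0.95.

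These ranges rest on assumed correlations from 0 to 0.95. The power range also assumes 80% power for absolute NCV, for which the article gives no effect or SD. The sample-size arithmetic itself is correct.

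**What to change.** Before any between-group results are seen:

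1. Name one primary test: the between-group difference in 12-month change in percentage NCV (the variable that was sized), in one stated segment, for example the entire index segment.
2. Test absolute NCV in the same segment next, in fixed sequence at 0.05, only if the first test is significant.
3. Label the 10-mm analyses supportive.
4. Align the abstract, objectives and hypotheses, endpoint and analysis sections with this definition.

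The stated 5% alpha and about 80% power then hold with 106 patients. This matters because recruitment already stands at 102 of 106.

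If the sponsor keeps two primary variables, use Holm and restate power per variable as about 70% at the first step (alpha 0.025), with an effect and SD justified for absolute NCV. The segment must still be named.

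The cost is about one paragraph and no extra patients. The downside is that absolute NCV and the 10-mm segment can no longer carry a positive claim on their own.

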## Methods/design

### Study design and subjects

This is a prospective, open-label, randomized, multi-center trial to investigate the efficacy of statin plus fenofibrate treatment compared to treatment with statin alone in non-diabetic, combined dyslipidemia patients with non-intervened intermediate CAD.

A brief flowchart of the study is summarized in Fig. 1.

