### Research materials

#### VH-IVUS and quantitative coronary angiography

VH-IVUS using a synthetic-aperture-array, 20-MHz, 3.2-French catheter (Eagle Eye, In-Vision gold, Volcano Corp, rancho Cordova, CA, USA) with motorized catheter pullback (0.5 mm per second) after intracoronary administration of nitroglycerin 0.2 mg will be performed in non-culprit lesions with intermediate stenosis. During pullback, grayscale IVUS is recorded and raw radiofrequency data are captured at the top of the R wave for the reconstruction of the color-coded map by a VH-IVUS data recorder (Volcano Therapeutics). Enrolled lesions will be native vessels and should be located more than 10 mm apart from the intervened lesion. Cases where the patients’ condition is unstable or the characteristics of the lesions make it difficult to perform VH-IVUS in terms of severe angulated lesions, calcified lesions, or thrombus containing lesions, will be excluded.

Data from the VH-IVUS and CAG will be measured by an independent investigator who is blinded to patient group and characteristics. Data from VH-IVUS, such as percentage and absolute NCV, DC volume, F volume, FF volume, and presence of thin cap fibroatheroma (TCFA), and data for the gray IVUS, such as external elastic membrane, lumen, plaque volume, and the remodeling index, will be measured in the entire index segment and the most severe 10 mm segment centered on the minimal lumen area at baseline and after 12 months.

Data from CAG, such as reference vessel diameter, minimal lumen diameter, and lesion lengths, will be measured by a dedicated quantitative coronary angiography (QCA) program.

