#### Endpoint Adjudication Committee

The Endpoint Adjudication Committee (EAC) comprises interventional and non-interventional cardiologists who do not participate in the study. This will be in charge of the development of specific criteria of endpoints based on study protocol and will review the accuracy and adequacy of reported endpoints.

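### The safety endpoint is worded as reactions to the study drugs in an open-label trial, so knowledge of the arm can influence which events, chiefly myalgia, are counted

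*Protocol article*

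**What the plan says.** All references are to the protocol article.

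- **Endpoint.** Study endpoints lists, as secondary endpoint 6, "adverse reactions to the study drugs, including myalgia, elevation of CPK more than twice the upper limit of normal". The list is open-ended. Its liver criterion is given as "hepatic dysfunction (alanine aminotransferase more than three times the upper limit of normal". Study objectives and hypotheses uses the same idea: "The incidence of drug adverse effects will be another secondary endpoint of the study".
- **Masking.** Study design and subjects states: "This is a prospective, open-label, randomized, multi-center trial". The section on VH-IVUS and quantitative coronary angiography masks the imaging: "Data from the VH-IVUS and CAG will be measured by an independent investigator who is blinded to patient group and characteristics". No comparable statement covers safety.
- **Oversight.** The Endpoint Adjudication Committee consists of cardiologists from outside the study. It develops endpoint criteria and "will review the accuracy and adequacy of reported endpoints"; whether it is masked is not stated. The Data Safety Monitoring Board section gives the board all cumulative safety data.
- **Analysis.** Statistical analyses has no rule specific to safety. Its general rule is "Categorical variables will be expressed as number or percentage and compared by" a chi-square or Fisher's exact test, and a p "value < 0.05 will be considered statistically significant".

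**The concern.** Two sections define the compared outcome by its cause and not by its occurrence. Whether a muscle complaint is a reaction to a drug is a judgement. Here patient and cardiologist both know whether one lipid drug or two are being taken. If complaints on the combination are more readily blamed on treatment, a difference can appear where there is none. If the cardiologist is confident that the combination is well tolerated, a real difference can shrink. The direction cannot be predicted from the documents.

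What is at stake is the tolerability comparison, a stated secondary endpoint of a trial that adds a second lipid-lowering drug. Part of what is counted could reflect expectation and not harm.

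**Working it through.** **1. What the trial was sized for.** Inputs from Sample size calculations: difference 4.78, SD 7.82, two-sided alpha 0.05, power 80%, dropout 20%.

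- n per arm = 2 × [(1.960 + 0.842) × 7.82 / 4.78]² = 42.01. The plan gives about 42; strict rounding up gives 43.
- 42 / (1 − 0.20) = 52.5, so 53 per arm and 106 in total, as stated.

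The figure reproduces. It was set for percentage necrotic core volume, not for safety.

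**2. Where attribution can act.**

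| Component | Criterion in the article | Exposure to unmasked attribution |
|---|---|---|
| Myalgia | None numeric | Direct |
| Unlisted reactions | None; the list is open | Direct |
| CPK | More than 2 × ULN | Only if a raised value must also be judged a drug reaction |
| ALT | More than 3 × ULN | Same as CPK |

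The text does not settle whether the causality step applies to the two laboratory components.

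**3. How far attribution could move the count.** Counted rate = true rate × probability that an event is attributed to a drug. All rates and shares here are assumptions. The chance of p < 0.05 is exact for Fisher's two-sided test, 53 per arm, summed over all pairs of counts.

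| True rates (combination v statin) | Share attributed | Counted rates | Chance of p < 0.05, true → counted |
|---|---|---|---|
| 20% v 20% | 80% v 50% | 16% v 10% | 3.0% → 8.8% |
| 20% v 20% | 90% v 50% | 18% v 10% | 3.0% → 14.3% |
| 20% v 10% | 50% v 80% | 10% v 8% | 21% → 2.5% |
| 20% v 5% | 60% v 90% | 12% v 4.5% | 55% → 16% |

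In the first row the counted ratio is 16/10 = 1.6 with no true difference. In the third a true doubling is counted as 10/8 = 1.25.

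**4. What a test can show at this size.** Exact Fisher power, two-sided 0.05, assumed rates:

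| Rates | 53 per arm | 42 per arm |
|---|---|---|
| 5% v 10% | 7% | 5% |
| 5% v 15% | 27% | 20% |
| 10% v 20% | 21% | 18% |

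Newcombe 95% intervals for the risk difference:

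- 5/53 v 5/53: p = 1.0, interval −12.1 to +12.1 points.
- 6/53 v 3/53: p = 0.49, interval −5.8 to +17.5 points.

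**The case against.** The strongest reply is that the article describes no event-by-event causality judgement. The phrase about reactions may be only a label for a list of criteria, two of which are laboratory thresholds. CPK and hepatic function are measured at baseline and 12 months in both arms alike. Causality procedures normally sit in the full protocol, which is not shown. This stands for CPK and ALT, and it confines the point mainly to myalgia and unlisted reactions. It does not remove the point, because the endpoint's wording is what the article itself fixes, in two places.

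The oversight bodies are a partial answer. The adjudication committee reviews endpoints that have been reported, so it may not recover a complaint that was never called a reaction. The monitoring board sees all safety data, but that does not change what endpoint 6 counts.

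Several stronger readings are tempting and are not supported:

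- *That harms are compared by p < 0.05 alone.* Numbers or percentages are also to be reported, the rule is a general one, and intervals may be specified in an analysis plan that is not shown.
- *That a non-significant result will be taken as evidence of safety.* No section says so, and Study limitations already acknowledges the small sample.
- *That the safety endpoint is meant to support the later large trial.* Study limitations ties that trial to plaque findings, not to tolerability.
- *That attribution bias would dominate the result.* The shares are assumed. In the 16% v 10% case the chance of a false positive reaches only 8.8%. For a true 20% v 10%, power is only 21% even with perfect counting, so small numbers limit that comparison before attribution does.

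**Conclusion.** The point holds as a defect in the definition of one secondary endpoint. The counted outcome is tied to drug attribution, the trial is open-label, and no masked assessment of cause is stated. The bias can run in either direction and bears mainly on myalgia and unlisted reactions; it reaches CPK and ALT only if the causality step is applied to them. Its size cannot be derived from the documents, so the attribution figures show what is possible, not what is expected.

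The lack of a stated confidence interval is a supporting matter of reporting and not an error in itself. The low power is simply the reason an interval would help. Overall this is a minor-to-moderate correction. It does not touch the primary endpoint.

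**What to change.** 1. In Study endpoints, redefine endpoint 6 as all new myalgia, CPK above twice ULN and ALT above three times ULN arising after randomisation, counted by randomised arm regardless of judged cause. Align the sentence in Study objectives and hypotheses. Present drug-attributed events, including unlisted reactions, in a supplementary table.
2. As a supporting step in Statistical analyses, or in the analysis plan if it is not already there, show each component as a between-arm risk difference with a 95% confidence interval (Newcombe, for example).

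The cost is a few sentences. The laboratory values are already planned. Myalgia needs every recorded report to be counted, whatever its judged cause. There are two downsides: background myalgia unrelated to either drug will somewhat dilute a true difference, and patients who know their arm will still decide what to report. The change removes the attribution layer only.
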